### Eligibility criteria for patients

The eligibility criteria for patients are as follows:

1. Aged 18 years and older.

2. A confirmed diagnosis of non-insulin dependent Type 2 diabetes for a minimum of two years.

3. Capacity to provide informed written consent (that is, as established by the primary healthcare professional responsible for the patient’s care).

4. Ability to write and converse in English (that is, patients who do not require the support of an interpreter).

Patients will be excluded if they are currently taking part in any other intervention research studies; are prescribed sulphonylureas; or have evidence of heart disease, musculoskeletal disorders or other disabling conditions that could be worsened by increasing levels of PA. A primary care data quality analyst from the North of England Commissioning Support Service will provide each primary care practice with system specific reports to enable them to identify patients who meet the eligibility criteria.

Patients registered at each participating practice who fulfil pre-defined eligibility criteria will be invited to participate in the study.

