Specific design decisions were made to limit the amount of missing data in accordance with published guidance [37]. The MaMT2D intervention was designed to be flexible and to accommodate individual differences; therefore, patients will be supported by primary healthcare professionals to identify their activity of choice, including frequency, intensity and duration to increase tolerability. Furthermore, MaMT2D was designed to be integrated into usual clinical care. Consequently, patients randomised to the MaMT2D intervention will receive the intervention components during their usual diabetes review appointments to reduce burden. Finally, an experienced research nurse employed by the Diabetes Research Network will collect clinical outcome data from electronic patient records during each data collection phase (that is, baseline, one, six and twelve months) to minimise the burden on participating healthcare professionals and practice personnel. Information from each participant consent form will be entered into a password protected data management system that will record consent preferences (for example, decision to participate or not in semi-structured interviews). Each practice will be randomised to the intervention or control group following receipt of informed written consent by all participating primary healthcare professionals.

Practices will be stratified based on list size (with three cut-off points: <3,280; ≥3,280 to 5,989; ≥5,990 to 10,453; and >10,454) and randomised to either the intervention or control group prior to identification and recruitment of patients.

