A nominated member of staff from each participating practice will be asked to identify all patients registered on their practice list who meet the eligibility criteria. An invitation letter printed on practice headed paper, a standardised patient information sheet and consent form [See Additional file 4: Patient Information Sheet Control Group; Additional file 5: Patient Information Sheet Intervention Group; and Additional file 6: Patient Consent Form] along with a pre-paid envelope will be mailed to all eligible patients. Patients who do not respond to the invitation within a six-week period will be mailed a reminder letter. Patients will be asked to provide informed written consent to attend four face-to-face appointments at their primary care practice; wear an accelerometer for seven continuous days, complete a study questionnaire and have clinical measures taken at each data collection time point (baseline, one, six and twelve months). In addition, separate consent will be sought to video record their consultations; to take part in semi-structured interviews with a researcher (to identify enabling factors and barriers to effective implementation of MaMT2D in primary care); and to take part in a focus group discussion with a researcher and other participating patients from their practice upon completion of the study (to gauge overall opinion of the intervention and study processes and procedures, including ways in which they could be improved). If patients decide to opt out of video recordings, interviews and focus group discussions, they can still remain in the main study. Consent from both the healthcare professional and patient are required before a video recording of a consultation can take place. The first two practices to provide informed written consent will enter the open pilot study described above. Each practice will be provided with a site file containing a copy of the trial protocol, patient information sheets and consent forms for reference purposes and a log for recording and monitoring patient recruitment, attrition and adverse events. If a drop-out or adverse event occurs, the contact person at the practice will be asked to contact a member of the study team to provide details. A log of all recruitment activity will be maintained by the study team and stored on a password-protected server at Newcastle University.

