### Primary outcome measures

1. An assessment of primary care practices and patient’s willingness to take part in the trial will be conducted by examining the proportion of practices and patients that were both eligible and asked to participate against those who actually agreed to participate.

2. The patient identification procedure will be examined to determine whether identification of eligible patients from practice lists was feasible, rates of eligibility and reasons for ineligibility.

3. Acceptability of the study design will be measured by the number of primary care practices and patients who take part and remain in the trial (that is, appointment attendance and intervention, data and study completion rates) and reasons for drop-out, where provided will be examined. In a situation where a patient does not attend an appointment but contributes data at a specific data collection time point, this information will be recorded.

4. Primary care practice and patient recruitment rates will be measured by the number who consent to be randomised divided by the number eligible to be randomised and the number taking part in the trial divided by the length of the recruitment period. The practice recruitment period begins when the first round of practice invitations are mailed out and ends when the last practice recruited is randomised. Patient recruitment begins when the first group of eligible patients is mailed their invitation letter and ends when the last patient recruited provides informed written consent.

5. Willingness to take part in video recordings of consultations, semi-structured interviews and focus group discussions will be assessed in both the intervention and control groups.

6. Adherence to the study protocol (fidelity assessment) and barriers/facilitators to effective implementation of MaMT2D in the primary care setting will be assessed throughout the trial period. A proportion of consultations will be video recorded to assess adherence to intervention components; and data collection completion rates will be monitored and recorded at each data collection time point. Semi-structured interviews with participating primary healthcare professionals and patients will be conducted to identify barriers and enabling factors to implementation of the intervention in routine primary care.

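### Patients are identified and consented after their practice's allocation is known, on arm-specific sheets, so the between-group estimates are open to recruitment bias

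*Protocol article*

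**What the plan says.** The order of steps is in the protocol article under Recruitment procedures, in the text after Figure 1. Practices are "randomised to either the intervention or control group prior to identification and recruitment of patients". After that, "A nominated member of staff from each participating practice will be asked to identify all patients registered on their practice list" who meet the criteria. The phase two section on recruitment procedures adopts the same process. The Blinding section says that professionals, patients and researchers all know the allocation; only the statistician does not.

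Two patient criteria need judgement (Eligibility criteria for patients). One is the exclusion for heart disease, musculoskeletal disorders or "other disabling conditions that could be worsened by increasing levels of PA". The other is capacity to consent, "as established by the primary healthcare professional responsible" for the patient's care.

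Two features restrain discretion. A data quality analyst from outside the practice supplies "system specific reports to enable them to identify patients who meet the eligibility criteria", and the invitation pack "will be mailed to all eligible patients", with a reminder to those who do not reply.

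The pack differs by arm; the additional files list "Patient Information Sheet Control Group; Additional file 5: Patient Information Sheet Intervention Group".

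Primary outcome 1 assesses willingness by "examining the proportion of practices and patients that were both eligible and asked to participate against those who actually agreed to participate". Primary outcome 4 divides the number consenting to randomisation by the number eligible for it, for practices and for patients. Neither mentions arm.

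**The concern.** In a cluster trial, randomisation balances practices. It balances patients only if they enter the trial in the same way in both arms. Here two entry steps follow open allocation.

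- **Eligibility.** Staff who know whether they will be promoting activity may read the activity-related exclusion differently. Table 1 adds a possible reason: Module 8 of the training gives intervention staff a flowchart for screening patients before activity, while control practices are offered the training only after the trial. The article does not say whether list screening comes before or after training.
- **Consent.** Patients accept or decline on different material, so both the uptake rate and the kind of patient who accepts may differ by arm.

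At stake are the interval estimates for physical activity and HbA1c (phase two Analyses), the aim of relating activity differences to consultation behaviour (Treatment fidelity assessment), and the recruitment figures carried to a definitive trial. Willingness to be randomised is part of the first primary objective, but no patient is asked before the practice is allocated. What is measured in patients is willingness to join a known arm.

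**Working it through.** The plan gives no figure to reproduce: no expected uptake, intra-cluster correlation (ICC) or SD. The finding rests on the sequence.

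| Step | Timing | Arm known to those deciding? |
|---|---|---|
| Practice and professional consent | before allocation | no |
| Practice randomised | – | – |
| Staff apply patient criteria | after | yes |
| Invitation to all eligible, arm-specific sheet | after | yes |
| Patient consent | after | yes |

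The concealment described under Randomisation and concealment of allocation protects the practice step only. For patients, the numerator of outcome 4 does not match this sequence.

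The rest illustrates scale. From the phase two Sample size section: 200 patients and up to 20 practices, so 200/20 = 10 per practice and 200/2 = 100 per arm. All other inputs are assumed.

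**1. Precision of a between-arm mean difference, in SD units.** Half-width = 1.96 × √(2/100 × DE), with DE = 1 + (10 − 1) × ICC.
- ICC 0: 1.96 × √0.020 = 0.277.
- ICC 0.05: DE = 1.45; 1.96 × √0.029 = 0.334.

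**2. Eligibility route.** Suppose one arm excludes an extra 10% of patients whose mean activity is 0.5 to 1.0 SD below that of those kept. The shift is share × gap: 0.10 × 0.5 = 0.05 SD to 0.10 × 1.0 = 0.10 SD. Relative to the half-width, this is 0.05/0.334 = 0.15 to 0.10/0.277 = 0.36.

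**3. Consent route.** Suppose motivated patients are 50% of one arm and 60% to 70% of the other, and differ from the rest by 0.25 to 1.0 SD. The shift runs from 0.25 × 0.10 = 0.025 SD to 1.0 × 0.20 = 0.20 SD, that is 0.025/0.334 = 0.07 to 0.20/0.277 = 0.72 of the half-width.

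**4. What an overall uptake rate can show.** Assume equal numbers invited per arm and 30% uptake overall: 200/0.30 ≈ 667 invited, about 333 per arm. The same overall rate fits 30%/30% (100 v 100 recruited), 36%/24% (120 v 80) and 40%/20% (133 v 67).

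**5. What rates by arm can show.** Half-width of the uptake difference = 1.96 × √(2p(1 − p)/n × DE), with n invited per arm, DE = 1 + (m − 1) × ICC and m invited per practice (20 practices).

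| Overall uptake p | n | m | ICC 0 | ICC 0.05 |
|---|---|---|---|---|
| 30% | 333 | 33.3 | 7.0 points | 11.3 points |
| 20% | 500 | 50 | 5.0 points | 9.2 points |
| 10% | 1000 | 100 | 2.6 points | 6.4 points |

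At 30% overall, a 40%/20% split (20 points) would be clear under either ICC. A 36%/24% split (12 points) would be clear at ICC 0 and only just outside the interval's half-width at ICC 0.05.

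**The case against.** Staff have less freedom than the sequence suggests. The search report comes from outside, everyone eligible is mailed, and the nominated staff member need not be the one who delivers the intervention. This stands, and it narrows the eligibility route to the criteria that need judgement. It does not touch the consent route.

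The trial is a descriptive pilot, not powered for a definitive analysis. Most of the illustrated shifts are small beside the sampling error, and the remark in Analyses that a larger trial may prove unnecessary is tied to a very large difference, which shifts of this size would not produce. This also stands, and it lowers the priority.

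Two stronger readings are tempting, and the documents support neither. A reader might infer that recruitment rates will be pooled and so conceal an arm difference. Outcomes 1, 2 and 4 do not mention arm, but nowhere does the article say that the rates are pooled. Outcome 2 covers eligibility rates and reasons for ineligibility, practices and the study team keep recruitment logs, CONSORT reporting is promised, and the analysis plan may give the breakdown. A reader might also infer that staff will apply the exclusion differently in the two arms. The article shows only that they could.

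**Conclusion.** The concern holds as a design weakness. Eligibility decisions and consent both follow unblinded allocation, so randomising practices does not by itself make the patient groups comparable, and the between-group intervals are open to recruitment bias. For patients, the wording of outcome 4 does not fit the procedure.

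The size is unknown. The 0.025 to 0.20 SD range and the uptake splits rest wholly on assumed shares, gaps, rates and ICC values; they show what is possible, not what is expected. The pilot's feasibility aims survive, so this is a worthwhile low-cost correction and not a condition for the trial to proceed.

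**What to change.** 1. **Practices not yet randomised.** Run the analyst's report, apply all exclusions, then lock and date the invitation list before the allocation is released. This reorders existing steps and fits the two-stage practice recruitment. It costs a short delay to each randomisation. It closes the eligibility route but not the consent route. Eleven practices were randomised at submission; if all count towards the maximum of 20, at most 9 can benefit, and the pilot will contain two identification procedures, so record which practices had locked lists.

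2. **All practices.** For outcomes 1, 2 and 4, give the numbers eligible, excluded (with reason), invited and consented by arm, from the existing logs, with the arm difference and a 95% CI that allows for clustering by practice. The cost is one table.

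3. **Outcome 4.** Define the patient rate as consent to take part in a practice already allocated, and keep consent to randomisation for practices.

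4. **Analyses.** State that the between-group estimates are open to recruitment bias and should be read so when the definitive trial is planned.

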### Movement as Medicine for Type 2 Diabetes: Components of the intervention

This multifaceted behaviour change intervention comprises two distinct but interrelated components: an online training intervention programme for healthcare professionals and a primary healthcare professional-led intervention toolkit for patients.

### Healthcare professional online training intervention programme

The online training intervention programme presents eight distinct but interrelated modules that cover topics such as diabetes and metabolism, PA and exercise and the psychology of behaviour change. Module 7 is a dedicated ‘skills based’ module that aims to equip primary healthcare professionals with the skills to use pre-selected behaviour change techniques and behaviour change counselling skills listed previously to promote patient centeredness and increase PA behaviour in patients. Textual information, interactive features, video demonstrations, and consolidation quiz questions at the end of each core module aim to prepare primary healthcare professionals to confidently and faithfully deliver the primary healthcare professional-led intervention to participating patients. Once all content of the training intervention programme is viewed by primary healthcare professionals an online certificate will be generated to confirm completion.

Primary healthcare professionals employed by both primary care practices will complete the online training intervention programme component of MaMT2D. They will be emailed a unique login ID to access the password protected programme and will be given four weeks to complete all modules before using the intervention with patients. Ongoing access to the programme will be provided for the duration of the study and can be accessed at any time. Table 1 provides an overview of the MaMT2D online intervention training programme for primary healthcare professionals.

**Table 1 T1:** Components of the online training programme and their relationship to constructs within TPB and SCT

**Module**	**Form and information content**	**Theoretical constructs**
Module 1:	Video recording of a professor of movement and metabolism introducing the programme and providing details of how and why MaMT2D was developed	Symbolising (SCT)
Introduction to MaMT2D		Attitudes and beliefs (TPB)
		Subjective norms (TPB)
	Video recording of a Consultant Diabetologist and a Diabetes Specialist Nurse providing an overview of why PA is important for the management of T2D	
Modules 3 (metabolism & type 2 Diabetes), 4 (physical activity in the care of type 2 Diabetes); and 5 (physical activity & exercise)	Evidence-based information about the role of metabolism, PA and exercise in the context of Type 2 diabetes	Symbolising (SCT)
		Attitudes/beliefs (TPB)
		Forethought (SCT)
		Intention (TPB)
Module 6:	Evidence-based information on the use of psychological theory and theory linked behaviour change techniques and counselling skills to change PA behaviour	Attitudes/beliefs (TPB)
Using psychology to change physical activity Behaviour		Forethought (SCT)
		Intention (TPB)
Module 7: Using behaviour change techniques to increase physical activity behaviour	Video demonstrations of a Diabetes Specialist Nurse demonstrating the use of behaviour change techniques and behaviour change counselling techniques in practice with a mock patient	Symbolising (SCT)
		Observational Learning (SCT)
		Perceived Behavioural Control (TPB) and Self-efficacy (SCT)
		Subjective norms (TPB)
Module 8:	Flowchart diagram demonstrating how to screen adults with T2D prior to PA/exercise	Self-regulation (SCT)
Screening before physical activity		Perceived Behavioural Control (TPB) and Self-efficacy (SCT)
End of module 3,4 and 5 quiz questions	Provides feedback on performance	Perceived Behavioural Control (TPB) and Self-efficacy (SCT)
Flowchart summary (crib sheet with prompts) of the protocol for use of the patient toolkit during diabetes review appointments	Prompts for healthcare professionals to use specific behaviour change skills and techniques	Symbolising (SCT)
		Perceived Behavioural Control (TPB) and Self-efficacy (SCT)
		Intention (TPB)
		Self-regulation (SCT)

MaMT2D, Movement as Medicine for Type 2 Diabetes; TBP, Theory of Planned Behaviour; SCT, Social Cognitive Theory. Module 2 of the online training intervention programme provided participating healthcare professionals with an overview of the research process, that is how MaMT2D will be evaluated. It was not designed to target any theoretical constructs and as such was not included in Table 1.

### Primary healthcare professional-led intervention toolkit for patients

Patients will, in addition to usual clinical care, receive the primary healthcare professional-led intervention that involves support from a trained primary healthcare professional to use a range of printed materials, DVD and pedometer (SW200, Yamax Corporation, Tokyo, Japan) to help them to increase their everyday levels of PA. The printed materials comprise: 1) a discussion card presenting a decisional balance aid, importance and confidence rulers and a seven-day PA recall diary to enable individualised feedback to be provided on current PA behaviour (type, frequency, intensity and duration); and (2) a booklet to support patients through the process of short and long-term PA goal setting, action planning, self-monitoring towards their PA goal and encouragement to use rewards contingent on progress made towards a previously set PA goal. A menu of PA options is presented to encourage patient autonomy (that is, to consider what type of PA they would like to incorporate into their everyday lives), and activity planners and trackers are provided to allow patients to self-monitor the amount of time they spend active (or the number of steps taken each day) with reference to a predetermined PA goal (that is, patients will be supported to develop their own PA goals and plans and revise them based on their individual needs and preferences). Table 2 provides an overview of the content of the practitioner-led intervention.

**Table 2 T2:** Components of the healthcare professional-led intervention and their relationship to constructs within TPB and SCT

**Intervention component**	**Form and information content**	**Theoretical constructs**
Discussion card	Assessment of PA behaviour using a seven-day recall	Attitudes/beliefs (TPB)
		Forethought (SCT)
	A decisional balance aid to assess the pros versus the cons for changing PA behaviour	Intention (TPB)
		Perceived Behavioural Control (TPB) and Self-efficacy (TPB)
	Rulers assessing importance and confidence for change	
Booklet	Support to select an appropriate PA/exercise; set PA goals; consider means of social support; identify barriers/problem solve; set short and long-term goals; plan activity; self-monitor activity; prevent relapse	Forethought (SCT)
		Subjective norms (TPB)
		Intention (TPB)
		Self-regulation (SCT)
		Perceived Behavioural Control (TPB) and Self-efficacy (TPB)
Activity planners/trackers	Means to plan and monitor PA/exercise	Self-regulation (SCT)
DVD	Video recordings of adults with T2D engaging in PA/exercise and sharing their stories	Symbolising (SCT)
		Attitudes/beliefs (TPB)
		Observational Learning (SCT)
		Subjective norms (TPB)
		Perceived Behavioural Control (TPB) and Self-efficacy (SCT)
Pedometer	Device to monitor the number of steps taken each day	Self-regulation (SCT)
Record of progress pad	Record of readiness ruler outcomes; short and long-term PA/exercise goals; social support; potential barriers and ways to overcome them; self-monitoring method adopted; and activities of choice. Provides a mechanism for provision of feedback and an opportunity to monitor progress and recap during subsequent sessions	Perceived Behavioural Control (TPB) and Self-efficacy (SCT)
		Intention (TPB)
		Self-regulation (SCT)
Diabetes UK Leaflet	Leaflet entitled: Keeping active: an essential part of managing diabetes	Attitudes/beliefs (TPB)
		Perceived Behavioural Control (TPB) and Self-efficacy (SCT)
		Intention (TPB)

MaMT2D, Movement as Medicine for Type 2 Diabetes; TBP, Theory of Planned Behaviour; SCT, Social Cognitive Theory.

Patients will be invited to attend four face-to-face appointments with a participating primary healthcare professional from their practice (baseline, one, six and twelve months). Where possible, patients will see the same primary healthcare professional throughout the duration of the study to provide continuity. During these appointments they will be given a Diabetes UK leaflet and will receive the primary healthcare professional-led intervention. During each appointment the primary healthcare professional will complete a record of progress sheet to serve as a log of decisions made during each appointment (for example, whether a patient selected a preferred activity, set a PA goal and self-monitoring method). A carbon copy of the progress sheet will be retained by the primary healthcare professional to refer to during subsequent appointments. Materials will be used with all patients during baseline and one month appointments in both practices before any necessary changes are made. Once changes are made, the updated materials will be reintroduced and the study will continue to the 12-month intervention endpoint.

Follow up prompts have shown promising effects in behaviour change interventions while targeting a range of behaviours including physical activity [11,45,46]. Therefore, patients will receive a telephone call three months from baseline from a primary healthcare professional to ‘prompt’ PA behaviour. They will be asked if they have any questions regarding use of the intervention materials and offered support where needed to set or revise PA goals and receive individualised feedback based on performance where appropriate. At this time patients will also receive a ‘motivational’ card by mail from the research team thanking them for continuing to take part in the study and encouraging them to consider ways in which they could reduce their sedentary time and increase PA behaviour.

